### Data analysis

The intention to treat principle will be applied to all analyses (57). For all data we will use descriptive statistics to characterize and describe both the control and intervention arms. To confirm successful randomization, study arms will be compared with regards to age, sex and race/ethnicity distribution. Additionally, we will confirm that differences between the two arms do not exist for type of insurance and major comorbidities. If data is missing for variables under comparison to determine successful randomization, we will report the number of missing responses for each and show differences in between individuals with complete data and those with incomplete data across intervention arms, multiple imputation using the chained equations (MICE) method. Finally, logistic regression models will be used to adjust for baseline imbalances between groups. Comparisons will be made for categorical variables using a chi-square test or Fisher’s exact test, and for continuous variables, a two-sample t-test or Wilcoxon rank-sum test. We will use Bonferroni correction during our examination of baseline differences between treatment and control groups if analyses suggest differences between the groups, we will present adjusted model results rather than unadjusted results.

For primary and secondary outcomes that are proportions or binomial outcomes (percentage screened for SUD, number diagnosed with SUD, percentage diagnosed with SUD, number referred for SUD treatment, percentage referred for SUD treatment, HIV viral suppression, retention in care and kept visit proportion) a chi-square test or Fisher’s exact test and beta regression models will be used to compare the proportional outcomes in the trial arms. All significance testing will be two sided and use a level of 0.05.

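### Baseline significance tests decide whether adjusted or unadjusted results are presented, so the headline estimate, its scale and its covariates are not fixed in advance

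*Protocol article*

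**What the plan says.** All of the relevant text is in the Data analysis section of the protocol article, and it forms a sequence.

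- Purpose of the baseline comparison: "To confirm successful randomization, study arms will be compared with regards to age, sex and race/ethnicity distribution". It then adds two further items: "we will confirm that differences between the two arms do not exist for type of insurance and major comorbidities". The comorbidities are not listed.
- Tests named: "Comparisons will be made for categorical variables using a chi-square test or Fisher’s exact test". Numeric variables get a t-test or its rank-based counterpart.
- Multiplicity: "We will use Bonferroni correction during our examination of baseline differences between treatment and control groups". The number of tests is not given.
- Form of adjustment: "logistic regression models will be used to adjust for baseline imbalances between groups".
- Consequence: "if analyses suggest differences between the groups, we will present adjusted model results rather than unadjusted results".
- Level: "All significance testing will be two sided and use a level of 0.05".

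Two other sections matter. Randomization describes a simple 1:1 computer-generated allocation, concealed electronically and run by someone outside the research team. Sample size bases its power statement on an unadjusted two-sided chi-square test of 48% against 69%, with about 440 patients per arm. Nowhere does the article name a single primary analysis that holds irrespective of the baseline tests.

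**The concern.** A significance test at baseline asks whether a difference as large as the one seen could have arisen by chance. With concealed computer allocation that is already known: whatever difference appears is chance. A significant result does not show that randomisation failed, and a non-significant one does not show that the arms are the same.

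The test is also a poor way to choose covariates. What makes an imbalance important is its size together with how strongly the variable predicts being screened. The p-value reflects only the imbalance. A variable unrelated to screening can trigger adjustment, while a predictive variable with a moderate imbalance can be passed over. The Bonferroni step makes any triggering rarer but does not change the basis of selection.

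At stake is what the trial reports as its main result. One branch is a chi-square (or Fisher) comparison of percentages, naturally read as a difference in percentage points. The other is a logistic model, whose direct output is an odds ratio conditional on the covariates entered. The two are on different scales, and even on the odds-ratio scale an adjusted and an unadjusted value generally differ in a perfectly balanced trial. Because the comorbidities are unlisted, the number of tests, the corrected threshold and the possible covariates all remain open.

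**Working it through.** **1. The plan's own power figure.** Inputs from Sample size: 80% retention, 60% in-clinic screening, 40% portal completion, 440 per arm, two-sided 0.05.

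- Usual care: 0.80 × 0.60 = 0.48.
- Intervention: 1 − (1 − 0.48)(1 − 0.40) = 0.688, stated as 69%.
- Standard error under the null, with mean 0.585: √(2 × 0.585 × 0.415 / 440) = 0.0332. Under the alternative: √((0.48 × 0.52 + 0.69 × 0.31) / 440) = 0.0325.
- Power = Φ((0.21 − 1.96 × 0.0332) / 0.0325) = Φ(4.46), which is above 99.99%.

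The stated 99% is met; it would need only 198 per arm. The figure belongs to the unadjusted test.

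**2. How often the switch fires when randomisation is sound.** The number of tests k is not given. Taking k = 5 independent tests (age, sex, race/ethnicity, insurance, one comorbidity item) as an assumption:

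- With Bonferroni: 1 − (1 − 0.05/5)^5 = 1 − 0.99^5 = 4.9%. For k from 3 to 15 it stays at 4.9%.
- For reference, without the correction: 1 − 0.95^5 = 22.6%.

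So about 1 correctly randomised trial in 20 would present the adjusted result, and 19 in 20 the unadjusted one.

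**3. Effect on the test.** Simulation of 6,000 trials per scenario, n = 880, five independent standard normal covariates, each with log odds ratio 0.3 (moderate) or 0.6 (strong) for the outcome. The number and strength of the covariates are assumptions.

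| Analysis | Type I error, moderate | Type I error, strong |
|---|---|---|
| Always unadjusted | 5.5% | 4.9% |
| Always adjusted | 5.4% | 5.3% |
| Bonferroni switch | 5.4% | 4.9% |

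The Monte Carlo standard error is √(0.05 × 0.95 / 6,000) = 0.3 percentage points, so none of these is distinguishable from 5%. With a conditional log odds ratio of 0.88 (odds ratio 2.41), power under the switch was 100% and 99.8%.

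**4. Effect on the reported number.** In the same simulations with a real effect:

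| Covariates | Mean unadjusted odds ratio | Mean adjusted odds ratio |
|---|---|---|
| Moderate | 2.23 | 2.43 |
| Strong | 1.93 | 2.43 |

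For weaker covariates the gap is small. Take a balanced binary covariate, 40% portal completion, and clinic screening of 53% against 43% in its two levels (assumed). The odds ratio is then 2.39 unadjusted and 2.40 adjusted. With 58% against 38% the adjusted value is 2.45. In both cases the risk difference standardised from the adjusted model is 20.8 points, equal to the unadjusted difference 0.688 − 0.48. Reporting a standardised risk difference therefore removes the change of scale.

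**The case against.** The strongest defence is that little goes wrong in practice. The trigger uses baseline data only, never outcomes. Bonferroni keeps it rare, so about 95% of sound trials would present the unadjusted chi-square result for which the trial is powered. Error rates hardly move and power is ample. The switch even has some logic: in the simulated null trials where it fired, the unadjusted test rejected in 8.2%, so those are trials in which adjustment is useful. An unseen statistical analysis plan might also list the covariates.

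Most of this stands and limits the severity. It does not rescue the rule. The article states that baseline analyses choose which result is presented, and that one replaces the other, so this is not a detail left to another document. A fixed adjusted analysis would deal with chance imbalance in every trial without any switch.

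A reader might go further in four ways that the documents do not support.

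- **That the switch invalidates the primary test or its error rate.** The simulated type I error of 4.9% to 5.4% does not show this.
- **That the odds ratio would jump when adjusted for clinic attendance.** With 80% attenders and clinic screening of 58% against 8% (assumed), it does move from 2.39 to 2.67. But attendance is not among the variables compared, so the rule could neither fire on it nor adjust for it. The 2.67 also pools very different stratum odds ratios: 2.15 in attenders and 9.33 in non-attenders.
- **That baseline viral suppression is a strong predictor of being screened.** The article lists it only as an outcome.
- **That every useful covariate is already in the data extract.** The article does not say what the extract contains.

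**Conclusion.** The point holds as a defect of pre-specification and should be corrected. The plan does not fix in advance which estimate is the headline, on what scale, or with which covariates, and it leaves that to tests that cannot do what they are said to do. The switch would operate in about 5% of correctly randomised trials, assuming independent tests and a number of tests fixed beforehand. How far the reported odds ratio would then move depends on how predictive the covariates are, which the article does not say. Under the assumptions tried it ranged from almost nothing (2.39 to 2.40) to substantial (1.93 to 2.43). The conclusion of the primary significance test is very unlikely to be affected, and the sample size need not change.

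**What to change.** Delete the baseline significance tests, the Bonferroni step and the sentence that makes the presented result depend on them. Present baseline characteristics by arm descriptively.

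Name one primary analysis that applies whatever the baseline shows. Either of these would do:

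1. the unadjusted difference in the percentage screened, with a 95% confidence interval and the chi-square test used in Sample size; or
2. a logistic model with a fixed list of covariates the plan already intends to compare (age, sex, race/ethnicity, insurance type), reported as a standardised risk difference with a 95% confidence interval.

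Report the other as a sensitivity analysis in every case. Option 1 is the smaller change, because it keeps the powered test as primary.

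Prior clinic attendance could be added to the fixed list if it can be exported from the health record. The arithmetic in Sample size makes clinic screening depend on retention in care, so attendance before randomisation is a plausible predictor.

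The cost is a few sentences and one additional analysis, plus a slightly larger data extract if prior attendance is included. Recruitment and sample size are unaffected.

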#### Intervention outcomes

The primary outcome is the percentage of PLWH who have had a clinic visit in the last two years in the Ryan White Clinic and who were screened for SUDs. Secondary outcomes include the number and percentage of PLWH diagnosed with SUDs, and the number and percentage of PLWH referred for SUD treatment. Secondary HIV care outcomes will include (1) retention in care measured as the kept visit proportion (the number of clinic visits attended divided by the number of clinic visits scheduled) in the 12 months after screening, and (2) HIV viral suppression, defined as a quantitative viral load <200 copies/mL in the year post-screening.

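### Beta regression is assigned to outcomes it cannot fit: the yes/no outcomes, and in its ordinary form the kept-visit proportion

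*Protocol article*

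**What the plan says.** In the protocol article, Data analysis, one rule covers every outcome. It opens "For primary and secondary outcomes that are proportions or binomial outcomes (percentage screened for SUD, number diagnosed with SUD, percentage diagnosed with SUD", continues through the referral outcomes, and closes with "HIV viral suppression, retention in care and kept visit proportion) a chi-square test or Fisher’s exact test and beta regression models will be used". The stated purpose of the model is that "beta regression models will be used to compare the proportional outcomes in the trial arms". Nothing says which method belongs to which outcome.

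The Intervention outcomes section shows what the data will look like. The primary outcome begins "The primary outcome is the percentage of PLWH who have had a clinic visit in the last two years in the Ryan White Clinic" and counts those screened, so each patient is screened or not. Suppression is "HIV viral suppression, defined as a quantitative viral load <200 copies/mL in the year post-screening", again yes or no. Kept-visit proportion is different in kind: "the number of clinic visits attended divided by the number of clinic visits scheduled".

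The preceding paragraph of Data analysis gives a separate job to another model: "logistic regression models will be used to adjust for baseline imbalances between groups". The Sample size section rests the power on a two-sided chi-square test.

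**The concern.** The outcomes in the list are of two kinds: a 0/1 record per patient, and a per-patient ratio of small counts. Beta regression models a continuous response inside the open interval from 0 to 1. It therefore cannot use a 0/1 record at all, and it cannot use a kept-visit ratio for a patient who attended every scheduled visit or none.

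At stake are the effect estimates. A chi-square test gives a p-value but no effect size, so the regression is where an estimate and its interval would come from. If the named model will not run, the analyst must choose a substitute or a workaround once the data are in hand. For kept visits, neither named method suits the outcome, and the unit of analysis is not stated.

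**Working it through.** **1. The plan's own figure.** Inputs from Sample size: 440 per arm, 80% retention, 60% in-clinic screening, 40% portal completion.
- Usual care: 0.80 × 0.60 = 0.48.
- Intervention: 0.48 + 0.52 × 0.40 = 0.688, stated as 69%.
- Power of a two-sided chi-square test at 0.05 with 440 per arm: above 0.9999, against 99% stated. About 200 per arm would give 99%.

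The stated power is met, and it does not depend on beta regression.

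**2. Beta regression on 0/1 data.** With mean μ and precision φ, the log-density contains (μφ − 1)·log y + ((1 − μ)φ − 1)·log(1 − y). At y = 0 the first logarithm is −∞; at y = 1 the second is. With μ = 0.48:
- φ = 4 or 10: both multipliers are positive (φ = 4 gives 0.92 and 1.08), so the log-density is −∞.
- φ = 1: both multipliers are negative (−0.52 and −0.48), so it is +∞.

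Every record is 0 or 1, so no finite likelihood exists. A standard beta regression routine rejects such data. Using the arm-level percentages as the response does not help: that gives two observations for three parameters (intercept, arm effect, precision).

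**3. What a forced fit would return.** The document does not propose this step; it only shows what the obvious workaround would do. Take 211/440 and 304/440 screened (48% and 69%).
- Observed odds ratio: (304/136) / (211/229) = 2.235 / 0.921 = 2.43.
- Moving 0 and 1 inward by constants from 1e-6 to 1e-2, the fitted means are 0.489 and 0.596–0.600.
- Odds ratio: (0.596/0.404) / (0.489/0.511) = 1.54, up to (0.600/0.400) / (0.489/0.511) = 1.57.
- Difference: 11 points instead of 21.

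**4. Boundary values in kept-visit proportion.** The document gives neither visit counts nor a keep rate. Assume m scheduled visits, each kept independently with probability 0.75. Then P(ratio is exactly 0 or 1) = 0.75^m + 0.25^m.

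| m | Share at 0 or 1 |
|---|---|
| 2 | 0.5625 + 0.0625 = 0.625 |
| 3 | 0.4219 + 0.0156 = 0.4375 |
| 4 | 0.3164 + 0.0039 = 0.320 |

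Correlation between a patient's visits raises the share. In simulation with 2–6 visits and an intraclass correlation (ICC) from 0 to 0.5, it was 30–64% at a mean of 0.7 and 44–72% at a mean of 0.8.

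**5. Chi-square on kept visits.** The answer depends on the unit.
- Visits pooled as independent, 4 per patient, ICC 0.1–0.3 (assumptions): design effect 1 + 3 × ICC = 1.3–1.9. True type I error is 2·P(Z > 1.96/√1.3) = 0.086 to 2·P(Z > 1.96/√1.9) = 0.155.
- Simulation under no difference, 440 per arm, 2–6 visits, mean 0.8: 0.05 at ICC 0, 0.10 at 0.1, 0.14 at 0.2 and 0.18 at 0.3.
- Patient as unit, ICC 0.3: a chi-square across the distinct ratios rejects 0.046 of the time, and one dichotomised at 0.75 rejects 0.054. Both hold the nominal level.

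**The case against.** The best defence is that the sentence can be read with each method going to its own type: chi-square/Fisher for binomial outcomes, beta regression for true proportions. A condensed article may also leave boundary handling to a fuller document. This reading is possible but does not remove the defect. The article calls the primary outcome a percentage, so it could fall under either label. Under the kindest mapping, the only true proportion is kept visits, and ordinary beta regression fails there as well. This is a method stated wrongly, not a detail left out. What stands is that a zero/one-inflated or boundary-adjusted beta model would be legitimate for kept visits, had it been named.

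Four stronger readings are tempting and are not supported:
- *The primary analysis is invalid.* It is not. The chi-square test named in the same sentence is valid and matches the power calculation.
- *Half the effect will be lost.* That needs the squeezing step in item 3, which the document nowhere proposes. Software would reject the raw data openly, and the raw percentages and the chi-square would still show the difference.
- *The kept-visit test has inflated type I error.* That holds only if visits are pooled as independent and are correlated within patients. The article states neither the unit nor a correlation.
- *Two incompatible models are given for the primary outcome.* Logistic regression is named for a separate task, adjustment for baseline imbalance.

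**Conclusion.** The point holds in limited form. As written, beta regression is attached to yes/no outcomes that it cannot fit, and this needs no assumption. In its ordinary form it also fails for kept-visit proportion. The share of patients affected there, about 32–63%, assumes 2–4 scheduled visits and a 75% keep rate.

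The consequence is confined to the model-based effect estimates and the kept-visit analysis; the primary test, the sample size and the power stand. Two figures are conditional illustrations, not properties of the plan: about 49% vs 60% (OR about 1.55) instead of 48% vs 69% (OR 2.43) if a fit were forced, and a type I error of about 9–16% if kept visits were pooled with 4 visits per patient and an ICC of 0.1–0.3.

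**What to change.** Replace the single rule in Data analysis with one line per outcome type.

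- **Screened, diagnosed, referred, virally suppressed:** keep chi-square or Fisher's exact as the test. Replace beta regression with patient-level logistic regression, which the section already names for adjustment, or with log-binomial or modified Poisson regression. Report a risk difference or risk ratio with 95% CI.
- **Kept-visit proportion:** state that the patient is the unit. Replace chi-square and ordinary beta regression with a method that accepts 0 and 1, for example a binomial model of attended out of scheduled visits with patient-level robust variance, a fractional logit or a beta-binomial model.

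The cost is a few sentences. Standard software suffices, no new data are needed, and the sample size does not change. The change should be made before outcomes are analysed, so that the model is not chosen in view of the results.

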## Discussion

PLWH are disproportionately affected by comorbid SUDs, which leads to negative health outcomes, potentiated by the fact that SUDs are underdiagnosed and often not treated among PLWH. Currently, limited evidence exists describing the optimal screening strategy for SUD among PLWH. Our approach will be one of the first to incorporate the privacy and convenience of a patient portal-based SUD screener compared to the current standard of care: in-person screening during routine clinic visits. Our method allows patients to self-report data, which then is automatically relayed to the patient’s primary HIV clinician, thus potentially increasing sensitivity of screening and both standardizing and improving documentation of screening results. Furthermore, we are screening for SUD among a population of PLWH who have historically received care at the clinic, as a population health approach, which differs from the reactive approach of screening during visits. This will allow the opportunity to reach PLWH who may not attend clinic visits. Also, because ePORTAL HIV-S is being implemented pragmatically within a large, real-world medical home, it allows us to test our intervention’s effectiveness and implementation strategy within the context of existing clinical practice. SUD remains one of the biggest challenges facing healthcare today, across diverse populations (15, 58, 59). We believe that the results of this study–and the fundamentals of ePORTAL HIV-S, including confidential, convenient online screening and incorporation of a CHW–will be potentially applicable to broader populations at risk for SUD. It will provide crucial information regarding the effectiveness of portal-based screening for SUD. Our findings may also have implications for screening for other behavioral or mental health conditions, or other conditions that may be associated with stigma.

## Limitations

Our findings may not be generalizable in settings where there are significant differences in cultural mores related to substance use, HIV, and stigma compared to ours. Additionally, our findings are contingent on patients’ access to private personal electronic devices with internet access. Finally, our health system has access to behavioral health services, a CHW, and clinician collaboration, which may not generalize to other settings, particularly ones without access to EHR technology or low-resource medical settings, including other countries.
